**Figure 1 figure1:**
[figure not shown]
Study design. AE: adverse event; COC: combined oral contraceptive; FSFI: Female Sexual Function Index; GAGS: Global Acne Grading Scale; POMS: Profile of Mood State; VAS: visual analog scale.

Parameters evaluated in blood samples in the subgroup of participants from Genoa.
**Metabolic**
GlucoseInsulinTotal cholesterolHigh-density lipoprotein cholesterolLow-density lipoprotein cholesterolTriglycerides
**Endocrine**
Total testosteroneDehydroepiandrosteroneAndrostenedioneSex hormone–binding globulinFree androgen index
**Related to coagulation**
FibrinogenFactor VIIAntithrombin IIIFactor VIIIProtein CThrombin timeAnticoagulant functional protein CTotal protein SActivated protein C resistance

**Table 1 table1:** Cycle evaluation parameters.

Parameter	Normal	Abnormal
Frequency	≥24 and ≤38 days	Absent (no bleeding): amenorrhea Infrequent (>38 days)
Duration	≤8 days	Prolonged (>8 days)
Regularity	Regular (shortest to longest cycle variation: ≤7 to 9 days^a^)	Irregular (shortest to longest cycle variation: ≥10 days)
Flow volume (participant determined)	Participant considers normal	Participant considers light Participant considers heavy
Breakthrough bleeding (bleeding or spotting between the cyclically regular onset of menses)	None	Random Cyclical (predictable): Early cycle Mid cycle Late cycle
Unscheduled bleeding on progestin±estrogen gonadal steroids (contraceptive pills, rings, patches, intrauterine contraceptive devices, or injections)	None (for a participant on gonadal steroid medication) Not applicable for participants not on gonadal steroid medication	Present

^a^Normal variation depends on age; these data are calculated excluding short and long outliers.

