### End Points

The primary objective of the study is to investigate menstrual cycle control by evaluating breakthrough bleeding (ie, bleeding or spotting between the cyclically regular onset of menses) during the use of the monophasic NGM/EE 0.25/0.035 mg COC. This is measured by calculating the intermenstrual bleeding or spotting occurrence rate at the sixth cycle and comparing this with the rate at baseline.

Secondary outcomes include the change from baseline at visits 2 and 3 in other parameters of cycle control (frequency, duration, regularity, participant-determined flow volume, and unscheduled bleeding), GAGS score, POMS, FSFI, and dysmenorrhea severity based on the VAS rating. Adherence and contraceptive failure rate over the 6-month study period are also secondary outcomes, as are changes from baseline in the metabolic, hormonal, or coagulation parameters in the subgroup of participants from Genoa. Adherence is being evaluated as a percentage of tablets taken, based on the medication returned by participants at each visit. Contraception failure is defined as the proportion of women who become pregnant during the 6-month study period. The reasons for any contraception failure will be identified and listed (eg, discontinuation or poor adherence).

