### Statistical Analysis

Based on the previous large-scale study with NGM/EE 0.25/0.035 mg, the rate of breakthrough bleeding is expected to decrease from 4.5% before use to 3% after 6 cycles, and the rate of intermenstrual spotting to decrease from 9% to 4% [17]. Therefore, a sample size of 175 participants would have 80% power to detect a treatment effect on breakthrough bleeding at a 1-sided α level of 5%. To account for a potential dropout rate of 30%, we plan to screen 240 women for eligibility and enroll 228 participants, an average of 38 participants at each of the 6 centers.

Two datasets have been defined for analysis: the per-protocol set, which includes all participants with full treatment adherence and no major protocol deviations, and the intention-to-treat set, which includes all enrolled participants who received at least 1 dose of NGM/EE 0.25/0.035 mg. The primary outcome will be evaluated only in the per-protocol population to avoid any effects of noncompliance on the interpretation of this outcome. However, secondary efficacy outcomes and safety will be assessed in the intention-to-treat population using robust statistical methods against missing data, like linear mixed models.

Continuous variables will be described using the mean and standard deviation if they are normally distributed or using the median and interquartile range if nonnormally distributed. The distribution of these variables will be assessed using the 2-tailed Student *t* test for paired data or the Wilcoxon signed rank test. Categorical variables will be described using frequencies and percentages and compared using the chi-square test or Fisher exact test [25]. There will be no imputation for missing data, and data from unscheduled visits will not be included in the analysis. No adjustment for multiplicity will be made to adjust for a type I error in secondary end points. A *P* value of .05 is considered to be statistically significant.

All statistical analyses will be performed using the R statistical software (version 3.5 or later; R Foundation for Statistical Computing). The final analysis will be completed after all participants have completed the study, any queries have been resolved, and the database has been locked.

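### Flow volume is an ordered secondary outcome, but Table 1 groups light with heavy and the only test named for categorical variables ignores order

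*Protocol article*

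**What the plan says.** All references are to the protocol article.

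- **End Points** makes change from baseline at visits 2 and 3 a secondary outcome for "other parameters of cycle control (frequency, duration, regularity, participant-determined flow volume, and unscheduled bleeding". It names no favourable direction for flow.
- **Table 1 (Cycle evaluation parameters)** has a row "Flow volume (participant determined". The Normal column holds one level, "Participant considers normal". The Abnormal column holds two, "Participant considers light Participant considers heavy".
- **Procedures** uses Table 1 as the list of what participants record in the diary, so all three levels are collected.
- **Statistical Analysis** says: "Categorical variables will be described using frequencies and percentages and compared using the chi-square test or Fisher exact test". For secondary efficacy outcomes it adds that analysis is by intention to treat, "using robust statistical methods against missing data, like linear mixed models". It names no ordinal method and gives no scoring for flow.

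**The concern.** Light, normal and heavy form an ordered scale, and the question in a before-and-after study is whether women move along it and which way. The only classification in the article puts the two opposite ends in one column, and the only test named for categorical variables takes no account of order.

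Two readings are open, and neither suits the outcome.

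1. **Two classes, following the columns.** A woman going from heavy to normal leaves Abnormal, one going from normal to light enters it, and one going from heavy to light counts as unchanged. A consistent shift in one direction can therefore vanish, or appear as more or less abnormality, depending on where the women started.
2. **Three unordered levels.** Nothing cancels, but the statistic is the same for a shift and its mirror image, and power is lost against an ordered test.

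The Discussion names flow volume among the effects to be investigated, and there is no control group, so the before-and-after comparison is all the evidence on flow that the study will have. The issue is separate from pairing: a paired test on the two pooled classes would pool opposite changes in the same way.

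**Working it through.** The article gives no rate, effect size or power for flow, so there is no stated figure to reproduce. Every flow distribution below is an assumption.

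**Step 1. What each reading does to a shift.** Take 175 women at each time point. That number is borrowed for scale from "a sample size of 175 participants would have 80% power", which concerns breakthrough bleeding. The two time points are treated as independent, as a chi-square test would treat them. Counts are rounded to whole women and listed light/normal/heavy. The statistic is χ² = Σ(O − E)²/E. The ordered comparison is a linear trend test with scores 1, 2, 3: z = ±√[(N − 1)r²], where N = 350 and r is the correlation of score with time point.

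*Scenario A*, 10/60/30% to 30/60/10%: counts 18/105/52 to 52/105/18.
- Pooled: 70 of 175 Abnormal (40%) both times; χ² = 0, p = 1.
- Three levels: expected 35/105/35; χ² = 4 × 17²/35 = 33.0, p ≈ 7 × 10⁻⁸. Reversing the shift gives the same 33.0.
- Ordered: z = −5.74; reversed, z = +5.74.

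*Scenario B*, 10/70/20% to 40/55/5%: counts 18/122/35 to 70/96/9.
- Pooled: 53/175 = 30.3% to 79/175 = 45.1% Abnormal; χ² = 2 × 13²/66 + 2 × 13²/109 = 5.12 + 3.10 = 8.22, p = 0.004. Lighter flow appears as more abnormality.
- Three levels: χ² = 2 × 26²/44 + 2 × 13²/109 + 2 × 13²/22 = 49.2.
- Ordered: z = −6.93.

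*Scenario C*, 10/60/30% to 20/70/10%: counts 18/105/52 to 35/122/18.
- Pooled: 70/175 = 40.0% to 53/175 = 30.3% Abnormal; χ² = 2 × 8.5²/61.5 + 2 × 8.5²/113.5 = 2.35 + 1.27 = 3.62, p = 0.057. Lighter flow appears as less abnormality.
- Three levels: χ² = 23.2, p ≈ 9 × 10⁻⁶.
- Ordered: z = −4.61.

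All three shifts are toward lighter flow. Pooled, they read as nothing, a rise and a fall. Kept at three levels, all are detected, but without direction in the statistic.

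**Step 2. Power for a modest shift.** Assume 160 women with both measurements (228 × 0.7 = 159.6), a latent normal flow variable, within-woman correlation 0.3 to 0.5 and a two-sided 5% test. With a baseline of 15/65/20%, a shift of 0.3 SD toward lighter flow gives about 23/64/13%, so Abnormal goes from 35.0% to 35.8%. Simulated power:

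| Analysis | Power |
|---|---|
| Pooled Normal/Abnormal, exact McNemar | 4–5% |
| Three levels, unpaired chi-square | 52–55% |
| Three levels, paired, unordered (Stuart–Maxwell) | 65–74% |
| Three levels, paired, ordered score | 77–83% |

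The effect of order alone is the last row less the one above it: 77 − 65 = 12 points and 83 − 74 = 9 points. Across other assumed distributions with modest shifts, the ranges are 3–7% pooled, 19–54% for the unpaired chi-square, 31–75% for the unordered paired test and 40–85% for the ordered paired test. The gain from order alone is about 8 to 13 points. For large shifts every three-level test nears full power and the gain shrinks.

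With a 0.5 SD shift from the same 15/65/20% baseline, pooled Abnormal rises from 35% to about 39% although flow has become lighter.

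**The case against.** The strongest reply is that the article never says light and heavy are pooled for testing. Table 1 lists them as separate entries, and other rows also hold several entries under Abnormal; amenorrhea and infrequent bleeding are one example. A reader might infer that the plan makes a shift to lighter flow cancel out or read as worsening. The documents do not support that. It would follow only from a two-class analysis, which is not stated, and scenario C shows that even then it is not a general result. Nor does the unordered test cause cancellation: on three levels it detects all three shifts, and the planned frequencies and percentages would show their direction. Worsening also presumes a favourable direction, which the article does not give. This part of the objection stands in full.

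A reader might extend the point to bleeding duration, because Table 1 has a class "Prolonged (>8 days". That does not hold either. Statistical Analysis names paired tests for continuous variables and mixed models for secondary outcomes, and nothing says duration is analysed only through that cut.

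It can also be said that the mixed-model wording covers flow, or that an analysis plan not shown settles the coding. Possibly so. But the article gives no score for flow, a model fitted to Normal/Abnormal would still pool opposite changes, and the categorical test that the article does name is unordered.

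**Conclusion.** The point holds in a limited form. The article classifies an ordered secondary outcome so that its opposite ends share a heading, names only unordered tests for categorical variables, and leaves open whether flow is analysed at two levels or three.

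Under the two-level reading the loss is near total for the modest shifts assumed (power about 3–7%), and the apparent direction depends on the baseline mix. Under the three-level reading the loss is smaller: no direction in the test, and about 8 to 13 points of power with pairing held equal. The contrast between roughly 5% and 83% should not be quoted as the cost of what the plan states, because it combines pooling, which is not stated, with the ordering question.

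The sizes rest on assumed splits, shifts and correlations. The grouping, the secondary status of flow and the named tests come directly from the text. This concerns one secondary outcome and leaves the primary analysis untouched, but the improvement is nearly free and worth making.

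**What to change.** In the Statistical Analysis section, state that:

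- participant-determined flow volume is analysed at three ordered levels (for example light = −1, normal = 0, heavy = +1);
- change from baseline is tested with a paired ordinal method, either the Wilcoxon signed rank test on the change in level or a cumulative-logit mixed model over visits, with one of them named in advance (the mixed model sits more easily with the plan's aim of methods robust to missing data);
- the numbers shifting to lighter and to heavier flow are reported separately;
- the Normal/Abnormal grouping of Table 1 is used for description only and is not tested for flow.

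The cost is a few lines of text and one more model type. The three levels are already recorded, so no new data, visits or participants are needed. The change should be made before database lock.

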## Methods

### Recruitment

This prospective, open-label study is being conducted at 6 centers in Italy in healthy women aged 18 to 35 years who are starting oral contraception for the first time or planning to switch to a new COC for the purpose of contraception and not for therapeutic reasons. No specific tests are performed before enrollment, consistent with Italian guidelines that such tests are not indicated in women without individual or family risk factors [20]. Patients who are switching need to undergo a 1-month washout phase prior to entry by discontinuing their previous COC 1 month prior to starting NGM/EE 0.25/0.035 mg. The participants must be residents of Italy and be sufficiently proficient in Italian to understand the informed consent form and the instructions for COC use. The key exclusion criteria are contraindications to the COC according to the current summary of product characteristics, concomitant conditions that place users at risk of AEs, or the use of COC for indications other than contraception, such as polycystic ovarian syndrome, endometriosis, or recurrent menometrorrhagia. Complete inclusion and exclusion criteria are shown in Textbox 1. Certain concomitant medications are not permitted for the duration of the study to minimize the potential for drug interactions or confounding of end-point assessment (Textbox 1).

Complete inclusion and exclusion criteria.

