**Exclusion criteria (any 1 of these disqualifies an individual from participating)**
Any contraindications to the use of combined oral contraceptives (COCs) according to the current summary of product characteristics of Effimia, that is, women presenting (or having ever presented) with myocardial infarction, transient ischemic attack, stroke, angina pectoris, deep vein thrombosis, pulmonary embolism (or presence of blood clots in organs other than legs and lungs), any blood clotting disorder (such as protein C deficiency, protein S deficiency, and antithrombin-III deficiency), or who need to undergo surgery or lie down for a long period of time (including the risk of previous deep vein thrombosis, arterial thromboembolism, hypertension in the course of treatment, and diabetes). If any of the listed conditions should appear during the use of the tested COC, the product must be stopped immediately, and the participant withdrawn from the study.Severe diabetes with blood vessel damage, heart valve disease with complications, severe hypertension, severe hypercholesterolemia or hypertriglyceridemia, hyperhomocysteinemia, migraine with aura, hepatitis C (and taking medications for this condition), endometrial hyperplasia, or unexplained vaginal bleeding.Women who are breastfeeding or pregnant or suspect they are pregnant.Current or history of any liver disease not yet recovered (liver function not yet normalized), any benign or malignant tumor of the liver, any breast or genital organs cancer (even suspected), or jaundice during pregnancy or while using hormonal contraceptives.Galactose intolerance, total lactase deficiency, or glucose-galactose malabsorption syndrome.Hypersensitivity to the active substances or to any excipients of the tested COC (eg, norgestimate, ethinyl estradiol, or lactose).Use of any of the following during the study period (according to the summary of product characteristics of Effimia): treatments for tuberculosis (eg, rifampicin), epilepsy (eg, primidone, phenytoin, barbiturates, carbamazepine, or oxcarbazepine), HIV and hepatitis C virus infection (protease inhibitor drugs and nonnucleoside reverse transcriptase inhibitors such as ritonavir, nevirapine, efavirenz, and also ombitasvir, paritaprevir, or dasabuvir), fungal infections (eg, griseofulvin), arthritis, osteoarthritis (etoricoxib), or pulmonary arterial hypertension (bosentan), and St John's wort used as an antidepressant. Medicines containing cyclosporine, antiepileptic lamotrigine, tranexamic acid, theophylline (used to treat respiratory problems), and tizanidine (used to treat muscle pain or cramps) should not be taken as well.Use of hormonal contraceptives in the previous month.BMI ≥30 kg/m^2^ (class I obesity).Smoking >15 cigarettes per day.Off-label use of COC (eg, for polycystic ovarian syndrome, endometriosis, or recurrent menometrorrhagia).Currently taking part or who took part in clinical studies with experimental products in the previous month.Incapacity or inability to comply with the study protocol (unreliability in the intake of the product or in the completion of the diary) according to the investigator’s opinion.

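### Unscheduled bleeding has no applicable baseline under Table 1, so its planned change from baseline is undefined; its overlap with the primary breakthrough item also needs a counting rule

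*Protocol article*

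**What the plan says.** Four parts of the protocol article bear on this.

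- **Table 1, Cycle evaluation parameters.** The unscheduled-bleeding row covers bleeding on progestin with or without estrogen, contraceptive pills included. For women off such treatment the entry, printed in the Normal column, is "Not applicable for participants not on gonadal steroid medication". A separate row defines the primary item: "Breakthrough bleeding (bleeding or spotting between the cyclically regular onset of menses". That row has no restriction by hormone status.
- **Recruitment and Textbox 1.** One exclusion criterion is "Use of hormonal contraceptives in the previous month". Other entrants are starting oral contraception for the first time or switching, and "Patients who are switching need to undergo a 1-month washout phase prior to entry".
- **Procedures.** At the baseline visit women are asked about breakthrough bleeding and, as a further item, about unscheduled bleeding. Study pills are first handed out at that visit.
- **End Points.** The primary is the rate of intermenstrual bleeding or spotting at cycle 6 compared with baseline. Listed as secondary is "the change from baseline at visits 2 and 3 in other parameters of cycle control (frequency, duration, regularity, participant-determined flow volume, and unscheduled bleeding".

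**The concern.** A change from baseline needs a baseline. By the article's own definition the unscheduled-bleeding item does not apply to a woman who is off hormones, and the eligibility rules make every woman hormone-free at baseline. A listed secondary outcome therefore has no defined value for anyone. If software or a coder supplies a value anyway, the result will look like a finding about the pill when it only reflects the coding.

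The same table raises a second, smaller question, this time about the primary. Off treatment, a bleed between menses has one row to go in. On treatment it has two. The End Points section puts unscheduled bleeding among the other parameters of cycle control, which treats it as distinct from the primary item, but the article gives no rule for an event that meets both descriptions. With no control group, a recording difference that exists only on treatment would not cancel out.

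**Working it through.** The article states no figure for this point, so the check is a side-by-side reading with simple coding logic.

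**Part 1: is there a baseline?**

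1. Table 1: the item applies only while a woman takes gonadal steroids.
2. Textbox 1 and Recruitment: no hormonal contraceptive in the previous month; first-time starters, or switchers after washout.
3. Procedures: the study pill is first supplied at the baseline visit.
4. From 1 to 3, the number of women with an applicable baseline value is 0 of the planned 228.

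The coding then allows two outcomes. Let B be the baseline value and Y the value at visit 2 or 3 (0 = none, 1 = present), with change = Y − B.

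- *Not applicable treated as missing.* B does not exist for any woman, so there are 0 complete pairs. The Statistical Analysis section rules out imputation. The linear mixed models it names for missing data cannot estimate a change when the baseline is structurally absent for all participants.
- *Not applicable treated as normal.* B = 0 for every woman, so Y − B = Y, which is 0 or 1. The mean change equals the on-treatment proportion. In a paired table the cell for present at baseline and absent later is always empty, so no improvement can be shown.

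Under either coding, the only information in the item is the on-treatment proportion.

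**Part 2: which row takes an intermenstrual bleed?**

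| Time | Breakthrough row (primary) | Unscheduled row (secondary) |
|---|---|---|
| Baseline, off hormones | applies | not applicable |
| Cycle 6, on the pill | applies | applies |

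Let p be the true cycle-6 rate and f the share of cycle-6 events entered only in the unscheduled row.

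- Primary derived from the breakthrough row alone: recorded rate = p × (1 − f), so p × f is lost.
- Primary derived from either row: recorded rate = p, whatever f is.
- Events entered in both rows: f = 0, and nothing is lost under either derivation.

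The documents give no value for f and no information from which to estimate one. The loss could lie anywhere from zero upwards, so no magnitude is put on it.

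**The case against.** The strongest reply concerns the primary. A reader might infer from Table 1 that the cycle-6 rate will be understated and the reduction exaggerated. The documents do not support that. The End Points section defines the primary by the event, intermenstrual bleeding or spotting, and not by which row is ticked. Nothing makes the rows mutually exclusive. The diary form, the full protocol and the derivation rules are not shown and may already settle the matter. The net direction is not settled either: baseline comes from history taken at a visit and on-treatment data from a diary, and that difference could raise the recorded on-treatment rate. All of this stands. What remains is an overlap in the printed definitions that one sentence would close.

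On the baseline problem the reply is weaker. Switchers could report bleeding recalled from their previous pill. The article does not say this is intended, and it would still leave women with no earlier hormonal use without a value. Asking the question at the baseline visit, as Procedures describes, does not make the item applicable under Table 1. It is fair to add that this is one item in a list of secondary outcomes, and that no primary, sample-size or safety conclusion depends on it.

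**Conclusion.** The first part holds on the article's own wording. The change from baseline in unscheduled bleeding is undefined for all 228 planned women or, if not applicable is coded as normal, can only be zero or a worsening. This assumes that no participant takes gonadal steroids at baseline for a non-contraceptive reason, and that baseline means the hormone-free state at entry. The consequence is confined to one secondary outcome.

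The second part holds as an ambiguity only. On treatment the primary and secondary items overlap, at baseline they do not, and the article does not say how an event entered only as unscheduled is counted. Bias in the primary is possible but not shown. Its size is unknown, and it is zero if events are recorded in both rows or pooled in the derivation.

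**What to change.** 1. Remove unscheduled bleeding from the change-from-baseline list in End Points. Report it as an on-treatment proportion for each cycle with a 95% CI.
2. Keep the baseline entry as not applicable, separate from normal, so that it cannot enter an analysis as a zero.
3. State that the cycle-6 primary counts any bleeding or spotting outside the withdrawal bleed, recorded under either row. An event entered only as unscheduled then cannot lower the on-treatment rate. Applying the same rule at baseline changes nothing if Table 1 is followed, and picks up an intermenstrual bleed noted under the wrong item.
4. Check the diary form and the analysis plan. If they already contain such a rule, the third change reduces to a clarifying sentence.

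The cost is endpoint wording and derivation code, settled before database lock. No new data, visits or participants are needed.
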